### Assignment of interventions: blinding

#### Who will be blinded {17a}

The researchers, patients, and biostatistics expert will not be blinded.

#### Procedure for unblinding if needed {17b}

Since this study is designed open-labeled, there is no blinding method.

## Data collection and management

### Plans for assessment and collection of outcomes {18a}

#### Literature review

Databases such as Web of Science, PubMed, Elsevier, Scopus, and Medline, as well as the Google Scholar, will be explored for related studies on the factors affecting adherence to treatment in T2D patients.

#### Qualitative stage

In order to collect data for identifying factors affecting adherence to treatment in T2D patients, in-depth individual and semi-structured interviews with patients in Bandar Abbas will be used. In this step, the directed content analysis method will be used. After obtaining ethical approval and informed written consent from all participants, interviews will be conduct by first author. An interview guide (Table 1) is developed for the interviews, which includes demographic information and open-ended questions about the factors affecting adherence to treatment in T2D patients. In order to improve the quality of the interview guide, the opinions of the initial participants are applied in the interview guide. Each interview begins by asking the main questions of the interview guide based on Pender’s HPM constructs. Then, exploratory questions are asked to elaborate on the issue. Probing questions are also used when necessary; probing questions provide an opportunity for the researcher to guide the interview and focus on the points of ambiguity. The interviews will be done in a place where participants feel comfortable and interview time will be about 40–60 min.

**Table 1 Tab1:** Interview guide for the qualitative study

Opening questions	Probing questions
Please tell me about what is life like with diabetes?	What is the benefit of adhering to treatment as a diabetic person?
What factors influence your adherence to your treatment?	What are the barriers to adhering to treatment?
What do you know about the concept of adherence to treatment?	How capable you are of adhering to treatment?
	What do you feel about adherence to treatment?
	How effective are others to you about adherence to treatment?
	What effect does your work / living conditions have on your adherence to treatment?
	What do you do to commit to your treatment?

The rigor and credibility of the qualitative study will be evaluated according to Guba and Lincoln criteria [21]. The researcher will be engaged in the study process for a relatively long time. Findings and concepts will be shared with a number of participants to express their comments. Two out-of-study experts are asked to review the data. The researcher will use the maximum variation when selecting the study participants, and the study process will be explained in full detail.

#### Questionnaire design

The research team will categorize the results of the need assessment according to the constructs of HPM. Then, based on these categorized results, a treatment adherence questionnaire in accordance with HPM will design for T2D patients.

The questionnaire will be consisting of two parts: The first part is the demographic profile, which includes age, marriage, type of diabetes medication, age at the onset of diabetes, co-morbidities, and type of insurance covered. The second part will be based on constructs of HPM to measure adherence to medication, physical activity, and diet: perceived benefits of behavior, perceived barriers to behavior, perceived self-efficacy, activity-related affect, interpersonal and situational influences, immediate competing demands and preferences, commitment to plan of action, and health promotion behaviors.

The questionnaire, will be investigated and approved in terms of qualitative and quantitative content validity, face validity, construct validity through confirmatory factor analysis (CFA), and internal and external reliability.

#### Plans to promote participant retention and complete follow-up {18b}

Researchers will be in contact with participants through SMS and phone calls.

### Data management {19}

#### Qualitative stage

No name or surname in interviews (during the need assessment phase) will be recorded to protect the confidentiality of the participants’ information. After transcribing the interviews, the recorded information is deleted. The interview password-protected text is stored on a computer and is made only available to the first author. After gaining permission from the participants, all interviews are recorded using an audio-tape recorder and transcribed verbatim and then coded by the researchers through directed content analysis. The codes will be discussed, and finally, the codes will be categorized based on their similarities and concepts; therefore, them and sub them will make a construct according to HPM. Data management will be done by MAXQDA ver. 10.

#### Intervention stage

Training sessions during the intervention will be recorded using an audio-recorder that is encrypted and password-protected. Also, the files will transfer to a secure system. All identifiable data including any reference to the names or places will be removed from the data. Audio files will be saved in a separate password-protected folder and will be available only to the first author.

#### Confidentiality {27}

Participants’ personal identification information will be kept confidential and will be available to the clinic team and the first and second authors who will sign a non-disclosure agreement. Anonymous data will be available to other researchers of the study.

#### Plans for collection, laboratory evaluation, and storage of biological specimens for genetic or molecular analysis in this trial/future use {33}

There are no plans for collection, laboratory evaluation, and storage of biological specimens for genetic or molecular analysis in the current study and for future use in ancillary studies.

### Statistical methods

#### Statistical methods for primary and secondary outcomes {20a}

Data analysis will be performed using SPSS ver.26. To describe the quantitative variables, descriptive statistics will be conducted. In the intervention phase, independent *t*-test, paired *t*-test, and analysis of covariance are used to evaluate the effectiveness of the intervention on changing the behavior and HPM constructs.

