### Trial design {8}

This mixed-method study consists of 3 phases.

Need assessment as the first step aims to identify the factors affecting adherence to treatment in T2D patients. Different qualitative and quantitative data sources will be used for need assessment. After combining the results of the need assessment, a questionnaire based on HPM to measure adherence to medication, physical activity, and diet will be designed. In the next stage, based on earlier phases the intervention will be designed. The intervention phase with a superiority design is a randomized, open-label, parallel-group study. The participants will be randomly assigned at a 1:1 ratio to control and intervention groups. The intervention group will participate in an intervention program to improve T2D treatment adherence treatment (medication, diet, and physical activity) based on the Pender health promotion model. To evaluate the effect of the intervention, intervention and control groups will be tested for hemoglobin A1c (HbA1c) before and after the intervention.

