### Interventions

#### Explanation for the choice of comparators {6b}

The designed intervention will be carried out only by the intervention group and the control group will only receive routine clinical care. The control group will receive training at the end of the study.

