#### Outcomes {12}

The primary outcome is treatment adherence which will be measured according to score of the researcher-made questionnaire and HbA1c test before and 3 months after the intervention. Secondary outcomes include attendance at clinic appointments, weight, healthy diet days, and physically active days.

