#### Intervention stage

When designing the educational intervention, the two intervention and control groups will be selected from T2D patients with registered medical cases in the Diabetes Clinic of Shahid Mohammadi Hospital in Bandar Abbas. According to previous study [19], the pooled standard deviation is calculated to be 29.7. Also, assuming a type I error = 5%, test power = 80%, and also considering a 13.5-score difference in adherence to treatment of the intervention and control group, the sample size of each group is estimated to be equal to 76 [20]. Considering the 10% possible drop-out, the sample size is determined 83 people in each of the two groups.$$n=\frac{2{\left({z}_{1-\frac{a}{2}}^2+{z}_{1-\beta}\right)}^2{s}_p^2}{{\left({\mu}_1-{\mu}_2\right)}^2}=76$$

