#### Methods in analysis to handle protocol non-adherence and any statistical methods to handle missing data {20c}

In case of missing outcome data, the study analyses will be according to available data, relying on an assumption that data is missing at random. Reasons for missingness will be described by a chart, and frequency of miss patients for each stage will be described.

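### The within-arm paired t-test is listed as a test of effectiveness in a between-arm superiority trial; effectiveness should be judged by baseline-adjusted ANCOVA

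*Protocol article*

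**What the plan says.** Section {20a} of the protocol article gives one inferential task to three tests: "In the intervention phase, independent *t*-test, paired *t*-test, and analysis of covariance are used to evaluate the effectiveness of the intervention". Description of the quantitative variables has its own sentence just before, so the paired t-test is not offered there as description.

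The design is a between-arm comparison. Trial design {8} says "The intervention phase with a superiority design is a randomized, open-label, parallel-group study" and "The participants will be randomly assigned at a 1:1 ratio to control and intervention groups". Under {6b}, "the control group will only receive routine clinical care". The primary outcome in {12} is treatment adherence, "measured according to score of the researcher-made questionnaire and HbA1c test before and 3 months after the intervention". The intervention-stage sample size {14} rests on a 13.5-point difference between the arms with a pooled SD of 29.7, "assuming a type I error = 5%, test power = 80"%. It gives 76 per arm, raised to 83 for 10% dropout.

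On missing outcomes, {20c} says "the study analyses will be according to available data, relying on an assumption that data is missing at random".

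**The concern.** The arms are not matched, so the only pairing available is each patient's before and after values. A paired t-test therefore asks whether one arm changed over time. It estimates neither the quantity that {8} sets out to show nor the one that {14} is powered for.

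Change over time without any intervention effect is plausible here. Controls stay under routine diabetes care, every patient answers the same self-report questionnaire twice, and nobody is blinded. Any shift common to both arms then appears as a significant improvement in the intervention arm. Reading that as effectiveness would give a wrong conclusion far more often than the stated 5%.

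A smaller issue lies in {20c}. The missing-at-random justification covers all the analyses, but the listed tests do not share it equally. A model that conditions on baseline is valid when missingness depends on arm and baseline. A t-test on available cases is not always valid under that condition.

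**Working it through.** **Inputs from the protocol.** Difference 13.5, SD 29.7, two-sided 5%, power 80%, 76 evaluable and 83 enrolled per arm, 10% dropout (all {14}). **Assumed, because the protocol does not give them:** baseline-to-follow-up correlation r, a change common to both arms, equal SD at both times, and the dropout models. The 13.5 and 29.7 belong to the adherence score, so the figures below are for the score and not for HbA1c.

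**1. The plan's own figure.** n = 2(z₀.₉₇₅ + z₀.₈₀)² SD²/difference² = 2 × (1.960 + 0.842)² × 29.7²/13.5² = 2 × 7.849 × 4.840 = 75.98, so 76 per arm. This reproduces the stated number. The printed formula also squares the first z inside the bracket, which looks like a typesetting slip, since 76 comes from the standard form. The calculation is for a comparison of two independent means; no within-arm test enters it.

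**2. Paired test with no intervention effect, 76 per arm.** The SD of change is 29.7 × √(2(1 − r)), which is 35.1, 29.7 and 23.0 for r = 0.3, 0.5 and 0.7. The noncentrality is common change × √76 / SD of change, with 75 degrees of freedom. Chance that the intervention-arm paired test is significant:

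| Common change | r = 0.3 | r = 0.5 | r = 0.7 |
|---|---|---|---|
| 0 points | 5% | 5% | 5% |
| 5 points | 23% | 31% | 46% |
| 10 points | 69% | 83% | 96% |

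Simulation gave the same picture (24% to 46% at 5 points, 68% to 96% at 10). In the same simulated trials the independent t-test and ANCOVA each rejected in about 4% to 6%, whatever the common change.

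**3. Power of the two between-arm tests.** 83 × 0.9 = 74.7, about 75 completers per arm. Unadjusted: d = 13.5/29.7 = 0.4545, power 79.0%. ANCOVA: the effect becomes d/√(1 − r²) = 0.476, 0.525 and 0.568 for r = 0.3, 0.5 and 0.6, with power 82.6%, 89.1% and 93.3%.

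**4. Missing data.** With no effect and equal SDs, the expected available-case difference is r × (difference between arms in the mean baseline of completers). It is zero if dropout depends on baseline in the same way in both arms. Simulation with 83 per arm, 10% dropout and r = 0.5:

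- Dropout dependent on baseline equally in both arms (log-odds slope 1 or 2 per SD): bias of the independent t-test about 0.0 points, type I error 0.05.
- Dependent on baseline in the intervention arm only (slopes 0.5, 1, 2): bias about 0.6, 1.3 and 2.1 points, type I error 0.05, 0.06 and 0.07.
- Baseline-adjusted ANCOVA with one-arm dependence: bias below 0.1 point, type I error about 0.05 to 0.06.

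**The case against.** The strongest reply is that the list in {20a} is conventional shorthand: paired tests for change within arms, independent tests between arms, ANCOVA for the adjusted comparison. On that reading nobody intends to claim superiority from a paired test, and an analysis plan that is not shown may name the primary model. It is fair that the absence of a named primary test in a condensed article is not itself an error. But the sentence does more than omit a hierarchy. It says that the paired test is used to evaluate effectiveness, and that statement conflicts with the design.

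Four stronger readings are tempting, and the document does not support them.

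- A reader might infer that success may be claimed if any one of the three tests is significant, or if the intervention arm is significant and the control arm is not. No such rule is written.
- A reader might infer that {20c} is wrong, or that available-case t-tests always need missingness unrelated to baseline. Section {20c} covers all the study analyses, ANCOVA included, and the assumption suits a baseline-adjusted model. The t-test is biased only when the dependence on baseline differs by arm. The exclusion in {10} for missing more than two sessions can be triggered only in the intervention arm, so unequal loss is conceivable, but nothing says that it would follow baseline.
- A reader might call the unadjusted t-test an error or a loss of planned power. It is valid, and it delivers about the 80% that {14} planned. The ANCOVA gain is a benefit and depends on an assumed correlation.
- A reader might infer that ANCOVA is the only acceptable model. A mixed model with baseline, or multiple imputation including baseline, would also serve.

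**Conclusion.** The point stands in limited form. The paired t-test is listed for a purpose that it cannot serve, and the text should be corrected before analysis. Under no intervention effect and a shared change of 5 to 10 points, it would be significant in the intervention arm in about 23% to 96% of trials. That range rests on the assumed common change and correlation; with no common change the figure is the nominal 5%.

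The missing-data part is secondary. At the planned 10% dropout and an assumed correlation of 0.5, the bias of the available-case t-test is about 0.6 to 2.1 points, against a target difference of 13.5, and only if baseline-dependent dropout differs between the arms.

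**What to change.** In {20a}, state that effectiveness is judged by the difference between arms at 3 months from ANCOVA, with the baseline value of the same measure as covariate. Name the adherence score and HbA1c explicitly: the present sentence mentions neither HbA1c nor the covariate. Apply the same model to a secondary outcome only where a baseline measurement exists; {12} states before-and-after measurement for the score and HbA1c, not for the secondary outcomes. Keep the paired and unadjusted t-tests as descriptive or supportive, and say that no effectiveness claim rests on them.

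In {20c}, tie the missing-at-random statement to this baseline-adjusted model.

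A fixed term for session group should not be part of this change. The groups of 15 to 20 are described for the intervention only, so such a term would be nested in that arm and the arm effect would not be separately identified.

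The cost is wording only. ANCOVA is already listed, both baseline measures are already planned, and the planned sample is sufficient.

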#### Interim analyses {21b}

There are no interim analyses planned.

#### Methods for additional analyses (e.g., subgroup analyses) {20b}

A subgroup analyses will be performed for insulin to oral anti-diabetic drugs administrations.

#### Methods in analysis to handle protocol non-adherence and any statistical methods to handle missing data {20c}

In case of missing outcome data, the study analyses will be according to available data, relying on an assumption that data is missing at random. Reasons for missingness will be described by a chart, and frequency of miss patients for each stage will be described.

#### Plans to give access to the full protocol, participant level-data and statistical code {31c}

The protocol can be accessed via Iranian Registry of Clinical Trials (IRCT20211228053558N1: https://www.irct.ir/trial/61741). Reasonable access to other documents can be gained by contacting the corresponding author.

### Oversight and monitoring

#### Composition of the coordinating center and trial steering committee {5d}

The research team (consisting of three health education and promotion specialists, one doctor of internal medicine and one biostatistics expert) will be the supervision of all aspects of the study, including the completion of the study to ethical standards.

#### Composition of the data monitoring committee, its role and reporting structure {21a}

The Research Committee of Hormozgan University of Medical Sciences will ensure the safety of the study participants by monitoring the ethical conduct of the study to also ensure that the study is conducted according to the protocol and that the data are collected appropriately.

#### Adverse event reporting and harms {22}

This is not applicable as this is a low-risk intervention and no serious adverse events (SAE) are expected to occur in this trial on adherence.

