#### Intervention stage

Eligible participants will be women or men, over the age of 80, need to express their consent to participate in the research and have registered a medical case in the Diabetes Clinic of Shahid Mohammadi Hospital as a patient with T2D and also live in Bandar Abbas.

The exclusion criteria also include participating in intervention sessions (absence of more than two interventional sessions) and not referring to the Diabetes Clinic of Shahid Mohammadi Hospital.

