#### Intervention description {11a}

The intervention will be designed based on HPM constructs for T2D patients. The emphasis of the intervention materials will be on predictors of behavior that have been identified based on the need assessment and a pre-test that will be performed using the researcher-made questionnaire. The first author will recruit participants, will explain the purpose and process of intervention, and will obtain their informed consent to participate. According to the intervention program, the participants will not receive any other relevant education or training during the intervention. Sessions will present by one health education and promotion specialist and one internal specialist medicine, experienced in T2D treatment adherence. Intervention including 10 educational sessions in groups of 15 to 20 patients will be a combination of online and face-to-face methods according to the intervention group conditions. The intervention will be using challenging lectures, educational video clips, posters and pamphlets, and the main content of the sessions will be to promote and improve adherence to treatment in the areas of medication, diet, and physical activity. In-person sessions will be set to an average of 45 min and online sessions to 15 min. The control group will receive training at the end of the study.

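### Adverse event reporting is waived because no serious events are expected, which leaves a trial of medication, diet and activity adherence with no planned adverse event data

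*Protocol article*

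**What the plan says.** All references are to the protocol article.

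- **Adverse event reporting and harms {22}:** the section consists of a single sentence, which says "This is not applicable as this is a low-risk intervention and no serious adverse events (SAE) are expected to occur". Provisions for post-trial care {30} likewise states that no harm is anticipated.
- **Intervention description {11a}:** the sessions are to "promote and improve adherence to treatment in the areas of medication, diet, and physical activity".
- **Methods for additional analyses {20b}:** the plan here is "A subgroup analyses will be performed for insulin to oral anti-diabetic drugs administrations". Insulin users are therefore in the trial population.
- **Outcomes {12}:** the primary outcome is adherence, measured by "score of the researcher-made questionnaire and HbA1c test before and 3 months after the intervention". The secondary outcomes are clinic attendance, weight, healthy diet days and physically active days.
- **Frequency and plans for auditing trial conduct {23}:** the supervisor checks that study records exist and are complete. The examples given are consent forms, eligibility criteria, and data collection and storage methods.
- **Composition of the data monitoring committee {21a}:** the university's Research Committee "will ensure the safety of the study participants by monitoring the ethical conduct of the study", and also oversees compliance with the protocol and appropriate data collection.

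**The concern.** The waiver is a stated rule. It cannot be read as detail left to a fuller document, because a fuller document that collected harms would contradict it.

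The reason given is narrower than the rule. Expecting no serious events does not address non-serious ones, and recording is what would test the expectation. The low-risk judgement was also made before the programme's content existed: Trial design {8} and Intervention description {11a} say that the sessions will be built from the needs assessment and a pre-test.

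What is at stake is how the result can be read. If the programme works, patients on glucose-lowering drugs will take them more regularly while changing diet and activity. A fall in HbA1c would count as success. The trial could not say whether it came with more hypoglycaemic episodes or injuries. The abstract and the Discussion offer the results for diabetes planning, and Dissemination plans {31a} names policymakers among the audiences.

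**Working it through.** **1. Does the reason cover the rule?** The rule is that adverse event reporting does not apply. The reasons are low risk and no expected serious events. The article gives no event rate to support low risk, and the second reason does not reach non-serious events.

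**2. Could harm data arise elsewhere in the plan?**

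| Place | What it yields | Adverse events? |
|---|---|---|
| Outcomes {12} | Questionnaire score, HbA1c, attendance, weight, diet days, active days | None listed |
| Auditing {23} | Consent, eligibility, data handling | None listed |
| Missing data {20c} | Reasons for missingness | Only if an event led to missing data |
| Data monitoring {21a} | Ethics, protocol compliance, data collection | No adverse event data supplied |

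Worsening HbA1c or weight would be seen. Hypoglycaemia would not be, because stronger glucose lowering appears in HbA1c as benefit. Injuries would not appear at all.

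**3. The plan's own sample size.** Sample size {14} gives an SD of 29.7, a difference of 13.5, a 5% type I error (two-sided by the printed quantile) and 80% power. The standard formula gives n = 2(1.960 + 0.842)² × 29.7² / 13.5² = 75.98, so 76 per group, as stated. For drop-out, 76 × 1.1 = 83.6, printed as 83. The total is 2 × 83 = 166.

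**4. What recording would tell us if no events occurred.** The exact one-sided upper 95% bound with zero events in n patients is 1 − 0.05^(1/n).

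- n = 83: 1 − 0.05^(1/83) = 3.5%
- n = 76: 1 − 0.05^(1/76) = 3.9%

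If 10% of 83 were lost, 83 × 0.9 = 74.7 would remain, and the bound would still be about 3.9%. With nothing recorded there is no bound.

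**5. The chance of seeing at least one event in an arm of 83.** The documents give no event rates, so the rates here are assumptions. The formula is 1 − (1 − p)^83.

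- p = 1%: 57%
- p = 2%: 81%
- p = 5%: 98.6%

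**6. Power to compare arms**, again with assumed rates p₁ and p₂, mean rate p̄, and two-sided 5%: Φ{[|p₂ − p₁| − 1.96√(2p̄(1 − p̄)/n)] / √([p₁(1 − p₁) + p₂(1 − p₂)]/n)}. For 5% versus 10% with n = 83 this is Φ{(0.05 − 1.96 × 0.0409)/0.0407} = Φ(−0.74) = 23%.

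| Assumed rates | 76 per arm | 83 per arm |
|---|---|---|
| 5% v 10% | 21% | 23% |
| 5% v 15% | 54% | 57.5% |
| 5% v 20% | 80.5% | 84% |

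Recording would describe harm and bound a zero count. It would not support a sensitive test between arms.

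**The case against.** The best defence is that this is group education by lectures, videos, posters and pamphlets. The background section defines adherence as following what a health care provider has already agreed with the patient, and the programme as described adds no drug. No document figure contradicts the low-risk judgement, and none gives a rate of hypoglycaemia or falls. Usual care continues, and an internal medicine specialist co-presents the sessions. This stands as far as it goes: the foreseeable risk is an inference from the programme's aims and population. It supports keeping the recording light, but does not turn an expectation about serious events into a reason to record none.

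Four stronger readings are tempting, and the documents do not support them.

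- **That the monitoring and harms sections contradict each other.** The committee text says how safety will be ensured: through ethical conduct, compliance and data collection. That is compatible with the waiver. The committee has work to do, but no adverse event data to do it with.
- **That the trial cannot detect any harm.** Worsening HbA1c or weight would show. The accurate statement is that there is no planned means of detecting adverse events.
- **That the patients are very elderly, so falls are the main issue.** The article does print "Eligible participants will be women or men, over the age of 80". Yet the rationale cites prevalence at ages 25–70, the qualitative stage (under the same printed limit) seeks variation in employment status, and the interview guide asks about work. The limit is probably a misprint and is a separate eligibility question. The point here stands without it.
- **That a harms table would settle whether lower HbA1c came with more hypoglycaemia.** The power figures show that it would not, unless the difference were large.

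A fair warning also stands about the remedy. Only the intervention arm attends sessions and receives missed-session calls, so events volunteered at those contacts would be over-counted in that arm.

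**Conclusion.** The point holds as a moderate one that should be acted on. The waiver rests on a reason that does not cover non-serious events, and nothing else in the article captures events such as hypoglycaemia or injury. Followed as written, 166 patients would yield no adverse event data from the sessions through the 3-month assessment, and any HbA1c benefit would be reported without them.

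In size, the loss is descriptive information: an upper bound of about 3.5% to 3.9% per arm if no events occurred, and a simple count by arm otherwise. The bound assumes that every patient counted is asked. The detection and power figures rest on assumed event rates. The sample size, primary outcome and primary analysis are unaffected.

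A reader might infer that the programme is unsafe, or that it will be recommended for regional use without safety data. The documents support neither: they report no harm, and they say only that results can inform planning and will be disseminated.

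**What to change.** Replace the statement in Adverse event reporting and harms {22} with a short plan:

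1. At the existing 3-month assessment, ask both arms the same few items on hypoglycaemic episodes, falls or injuries, and unplanned hospital visits since baseline.
2. Tabulate the answers by arm, with the number of patients asked, descriptively and without a formal test.
3. Forward the table to the Research Committee named in section {21a}, and say there that it receives these data.
4. Log events volunteered at sessions or calls and pass them to the committee for oversight only. Keep them out of the between-arm table, because contact is unequal.

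The cost is a few extra items, a simple log and one table. No new visit, staff or procedure is needed and the sample size does not change. The downside is that self-report in an open-label trial is open to recall and reporting differences between arms, which the report should state beside the table.
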